## Abstract

**Introduction::**

Rural sanitation deficits in the United States represent an important source of non-point source pollution and may present risks to public health. We propose an interrupted time series analysis to measure the effect of a town-wide sanitation expansion program on the release of pathogens to the environment. This work is expected to yield valuable insight into the potential for rural sanitation improvements to reduce pathogen releases and support public health and well-being.

**Methods::**

We will conduct a longitudinal baseline study including quantitative measurement of key enteric pathogens and fecal indicator bacteria adjacent to households lacking adequate sanitation. As households connect to a new sewerage system serving the entire community, longitudinal household sampling will continue until crossover is complete. We will include concurrent comparison sites with existing appropriate sanitation as well as sites never receiving the intervention to monitor secular trends in pathogen releases during the study period.

**Analysis::**

We will compare the concentration of culturable *E. coli* in the environment pre- and post-intervention using a time series regression analysis suitable for an interrupted time series. We will couple pathogen measurements with quantitative microbial risk assessment to estimate the potential effect of the intervention on infection risks via key exposure pathways. A linked pre-post survey will focus on self-reported quality of life measures among households connecting to the system.

**Ethics and dissemination::**

Informed consent will be obtained prior to data collection, with participants informed of study details and risks. Participation is completely voluntary, and identifiable data will be securely and separately stored from all other data. Each household will be offered a summary of their site-specific data. Deidentified results will be shared with the community in a public forum and published in peer-reviewed journals.

## Introduction:

### Background and Context

Sanitary sewer connections are unavailable for many rural or disadvantaged communities within the United States (1). Residents without access to sewer connections typically rely instead on onsite sewage disposal systems (OSDS) – typically conventional septic systems – though these systems are vulnerable to failure due to inappropriate design, inadequate maintenance, unsuitable soils, high water tables, and climate-related events (2). The *Transforming Wastewater Infrastructure in the United States* project, supported by Columbia World Projects, aims to address these issues by presenting alternative wastewater technology solutions that are suited for use in rural and under-resourced settings. As part of this project, the team is piloting the installation of a community-scale wastewater treatment and collection system in a small rural community located in the Black Belt region of Alabama.

Alabama’s Black Belt is named for the dark, fertile soil that covers 17 counties in central Alabama, including Barbour, Bullock, Butler, Choctaw, Crenshaw, Dallas, Greene, Hale, Lowndes, Macon, Marengo, Montgomery, Perry, Pike, Russell, Sumter, and Wilcox; this is sometimes expanded to include Lamar, Pickens, Bibb, Clarke, Washington, Monroe, Conecuh, and Escambia. While the region is characterized by a rich cultural heritage and is the birthplace of the Civil Rights Movement in the United States, economic development remains limited (3). The state of Alabama consistently ranks among the states with the highest poverty rates, and as of 2023, Alabama had the 8^th^ highest poverty rate in the country (4). The statewide poverty rate is 15.6%, while the average poverty rate of the counties that make up the Black Belt is 24%. Many Black Belt communities experience high poverty, poor health outcomes, and inadequate access to health care (4–6).

Alabama’s Black Belt has recently gained national attention for the region’s failing or nonexistent wastewater infrastructure (7,8). It has been estimated that only 50% of households in the Black Belt are connected to municipal sewer systems, as compared to the national average for the U.S., 75% (9). While municipal sewerage is the ideal strategy for wastewater management in most cases, costs are high, and this model is unworkable where low housing density does not allow for capturing economies of scale. Also, low-income communities already served by conventional municipal sewerage may lack the resources for reliable wastewater treatment and disposal. For example, a recent survey found that more than 1/3 of utility providers across the state of Alabama do not have the means to properly cover the cost of operation, which makes funding updates and maintenance to the systems impossible (10).

Onsite or decentralized sanitation systems are common where conventional sewerage does not reach. Over 40% of Alabamians use an onsite wastewater treatment system, including the majority of those living in the largely rural Black Belt (12). The design of decentralized wastewater systems varies widely, but by far the most common and usually cost-effective model is a conventional septic system. These systems consist of two main elements: a subsurface septic tank, retaining solids that must eventually be emptied, and a drain field that facilitates subsurface discharge of aqueous effluent to the soil. Since wastewater containment depends on keeping effluent discharges below the surface and therefore away from people who could be exposed, systems are designed based on soil permeability (13). When the production of effluent exceeds the capacity of the soil for infiltration, the system fails and wastewater can appear on the surface of the ground, presenting exposure risks to people and the environment. Conventional septic systems perform poorly in much of the Black Belt due to the region’s heavy clay soils that are impermeable to water, though they have been widely implemented. Recent estimates suggest that 40% - 90% of onsite sewage disposal systems in the Black Belt are functioning poorly or completely failing (14). Failing onsite systems can result in sewage back-ups into homes and yards. For instance, after an extreme weather event in 2017, 42% of survey participants in Lowndes County reported having raw sewage backing up into their homes from bathtubs, sinks, and toilets (15). A failing septic system can be expensive to repair or replace; as of 2025, the installation of an alternative system that can safely operate with low-permeability soils can cost up to $30,000 in this region (16). This is not financially feasible for many residents in the Black Belt, where many live at or below the poverty line (17–19).

Without reliable and affordable alternatives, many households use what is known locally as “straight piping.” Straight-piping consists of a pipe that transports untreated wastewater (black water and/or gray water) directly from the home to an uncontained pit, ditch, stream, waste field, or another “disposal area” where it is accessible to people and animals (16). The Alabama Center for Rural Enterprise claims that most straight pipes are less than 10 meters long, suggesting that discharge points are typically within close proximity to homes (15). It is difficult to find data that encapsulates the full scope of this issue since homeowners can face legal repercussions for discharging wastewater via straight pipes. The use of “inadequate sewage disposal systems” is a criminal misdemeanor in Alabama that could result in fines – as much as $500 for each citation – eviction, and – in some cases – arrest (7). Considering the barriers to municipal sewerage and failures of onsite sewage disposal systems and the gaps these create, there is a need for innovation in this space to identify technologies and infrastructure models suitable for rural regions such as the Black Belt.

### Description of Intervention

This protocol details an evaluation of an infrastructure intervention that attempts to overcome the barriers to conventional sewerage and on-site sewage disposal systems by implementing a cluster system approach in a small town in the Alabama Black Belt. While most households are connected to the county water supply, there is no municipal sewerage serving this community. Households will be served by both septic tanks that remove solids from the wastewater and a pump to convey the liquid effluent to a localized treatment system. These systems are typically referred to as a septic tank effluent pump (STEP) or liquid-only sewer. To replace failing septic systems, straight pipes, and other forms of surface discharge of wastewater, households (~140) within and adjacent to a planned service area will be offered connections to the STEP system under the local Governmental Utility Service Corporation (GUSC).

The infrastructure development is funded through the American Rescue Plan Act (ARPA) with funds allocated from the Alabama Department of Environmental Management to the University of South Alabama. Through this infrastructure project, participating households within this town will receive and be connected to individual onsite tanks (~1000 gallon) for collection of primary solids, with liquid-only effluent pumped via a small-bore sewer to a localized treatment system (Orenco AX-Max). The Orenco AX-Max is an above ground, modular unit that treats liquid effluent via a recirculating media filter. Treated wastewater effluent from the AX-Max units will be disinfected by ultraviolet radiation (UV) and discharged to a local creek that runs through town. Discharge permits will be obtained from the Alabama Department of Environmental Management (ADEM).

This infrastructure will be implemented across three phases. In Phase I, completed June 2024, one Orenco AX-Max Unit was installed at a university affiliated architecture program with student housing. During Phase II, the system will be expanded to include centralized community spaces and connections will be offered to residences within the town limits. In Phase III, connections will be offered to neighboring, unincorporated communities.

### Intervention Fidelity and Adherence

This infrastructure project is piloting a new approach to wastewater treatment in the Alabama Black Belt and intends to demonstrate that safe, reliable, and effectively managed wastewater services can result in positive environmental and health outcomes for small communities at an affordable cost (capital and operation and maintenance). The evaluation team is conducting an independent assessment of this project and its impacts on the community, and do not benefit from or have influence over the success or failure of the intervention. To assess the fidelity of this intervention, we will collect data on the installation and functionality of both the household septic tank effluent pump systems and the centralized treatment system. We will gather data on household connections and use thorough observational and self-reported sanitary surveys. We will assess the performance of the system through longitudinal environmental sampling at household and community levels.

### Research Objectives and Hypotheses

The evaluation team will examine the effects of the infrastructure project on environmental contamination, infection risk, and individual well-being. These elements are addressed in the following primary (Objective 1) and secondary (Objectives 2–4) research objectives:
Objective 1: Measure the density of fecal microbes (enteric pathogens and fecal indicators) released to the local environment at the household and community levels before and after the implementation of a community-wide sanitation system. Hypothesis: Community-wide sanitation will result in a reduction in the density of enteric pathogens and fecal indicators in the environment.Objective 2: Collect qualitative and quantitative data regarding the type and functionality of pre- and post-intervention sanitation infrastructure at the household level through participant-taken and observational surveys. Hypothesis: The community-wide sanitation system will result in a reduction in the prevalence of failing sanitation systems and straight-pipe discharge sites.Objective 3: Model the effects of the implementation of a community-wide sanitation system on the enteric infection risks associated with exposure to enteric pathogens and fecal indicators. Hypothesis: Community-wide sanitation will reduce infection risks associated with exposure to enteric pathogens and fecal indicators.Objective 4: Explore whether and how the changes in sanitation service affect the quality of life of the participants included in the study. Hypothesis: The intervention will improve the quality of life for participants.

## Methods and analysis:

We will collect repeated environmental and household samples (wastewater, soil, drinking water, and surface water) across six structured time points to evaluate changes before and after intervention implementation, as outlined in Figure 1. All samples will be cultured for *E. coli*, and all soil, surface water, and wastewater samples will be analyzed for pre-specified enteric pathogens and fecal markers using quantitative PCR (qPCR). In addition to environmental sampling, structured surveys are conducted at selected time points: a demographic survey at time point one, sanitary inspection surveys at time points two and five, and a well-being survey at time points three and six (Figure 1). Further detail on survey content and analysis is provided in the detailed objectives below. The study began in August 2024 and will conclude at least three months after the final household in Phase II is connected to the intervention, currently targeted for December 2026. Each household follows the same six-point sampling schedule, although the exact dates vary depending on when the intervention reaches each home.

### Interrupted Time Series

To evaluate the effectiveness of this sanitation intervention, we will assess changes in environmental fecal contamination, as indicated by levels of culturable *E. coli* in soil, as our primary trial outcome. Environmental sampling offers a direct measure of how human waste is being contained or released into the environment and is fit to capture the potential health and environmental benefits of improved sanitation infrastructure. While the study includes various ways to evaluate impact (surveys, infrastructure inspections, and qualitative data), this approach allows us to quantify environmental contamination in a way that reflects both function and exposure risk. We focus on *E. coli* as a fecal indicator because it is routinely used to assess sanitary conditions and potential health hazards and based on preliminary data showing elevated culturable *E. coli* counts in impacted soils and surface waters (20–22). We focus on soil as a primary medium of concern given the prevalence of straight pipes and other systems that discharge directly to the surface in this region (9). For the purposes of this study soil also offers a more localized matrix than surface water. Soil will be collected directly from a household’s property and better reflects onsite contamination. Surface water can be intermittent, weather-dependent, and influenced by upstream contamination, making it harder to attribute *E. coli* to a specific source or sanitation system.

We will use an interrupted time series (ITS) design, which allows us to assess both pre-intervention trends and any shifts in *E. coli* concentrations following the introduction of the new improved sanitation infrastructure. In an ITS, longitudinal observations are “interrupted” by an intervention, and observations span the post-intervention period. In the context of sanitation infrastructure expansion, the point of intervention is often staggered as improvements come online and households connect, rather than at a single time point, so participating households “crossover” to the intervention once connected (23). An ITS also includes a counterfactual, the continued projected trend in a hypothetical scenario in which the intervention was not put in place. This provides a comparison for the impact of the intervention by discerning any changes between the observed data and the counterfactual (23,24).

We chose to use an ITS instead of a randomized controlled trial because in the context of community-wide infrastructure projects, randomized trials are infeasible and may come with additional equity and ethical concerns, regardless of the fact that health effects specifically attributable to sanitation are variable across trials (25,26). To address concerns that may arise in the absence of a randomized controlled trial, we will include a minimum of 10 additional households from a neighboring community that has existing adequate sanitation and 10 more comparison households with poor sanitation that will not be connected to the intervention until after the conclusion of this study. These 20 comparison sites will allow estimates of (1) background levels of fecal microbes in sample matrices and (2) the influence of non-intervention-related factors (e.g., flooding) on the presence and quantity of sanitation-related microbes. The comparison sites, along with the fact that we are sampling at multiple time points before and after the intervention, will allow us to account for temporal and spatial variation in microbial density.

### Sample Size Calculations

We calculated a sample size for our primary outcome using a time series regression appropriate for an ITS design. Here we calculate the number of households, *n*, that will be followed longitudinally across the six sampling time points, *t*, (three before and three after the intervention) to detect a meaningful change in soil *E. coli* concentrations with 80% power at a 5% significance level. Equation 1 calculates the crude number of households, *m*, needed before accounting for clustering (27).

Equation 1
$$m=\frac{2{\left(z_{\alpha }+z_{Q}\right)}^{2}\sigma^{2}\left(1-\rho_{1}\right)}{ts_{x}^{2}d^{2}}$$

In this equation the term *σ*^*2*^ captures the total variability in *E. coli* concentrations across all locations and time points, while *s*
^*2*^ accounts for the variability in repeated measurements within the same location. The intraclass correlation coefficient, ρ_1_ reflects how similar those repeated measures are over time for a given household. Finally, the effect size, *d*, is the expected change in log-transformed *E. coli* concentrations in soil attributable to the sanitation intervention.

To estimate the values used in this calculation, we used log-transformed concentrations of *E. coli* ybbW in soil samples based on preliminary data from soil samples collected in Hale County in 2023 (22). For sample size calculations, we assumed that *E. coli* ybbW in soil could serve as a proxy for culturable *E. coli* in soil, based on a moderate positive correlation observed between the two measures in soil samples (Spearman’s ρ = 0.54, *p* = 0.03). The total variance, *σ*^*2*^, was calculated as 5.2 log (copies/gram)^2^ based on all available soil samples. The within-household variance, *s*
^*2*^, was estimated as 4.3 log (copies/gram)^2^ from a mixed-effects model including a random intercept for location. The intraclass correlation coefficient, *ρ*_1_, which reflects the correlation of repeated measurements within a single location over time, was estimated to be 0.16. The effect size, *d*, was defined as a 0.45-log (copies/gram) reduction in soil concentrations, which corresponds to 20% of the standard deviation of log-transformed values from the pilot data. We selected this threshold to reflect a small but meaningful reduction in environmental fecal contamination. Using these inputs and *t* = 6 time points per household, we calculated an intermediate value of *m* = 13 households needed before adjusting for clustering.

Equation 2
$$n=m*\left(\left(1+\rho_{2}\right)*\left(\text{k}-1\right)\right)$$

To account for clustering of soil samples within sites, we applied Equation 2 (27). The intracluster correlation coefficient, ρ_2_, used in this adjustment was estimated as 0.17 from a model based on the preliminary data set that included random intercepts for both location and sampling date. We define *k* as the number of observations within each visit—in this case, the total number of soil samples collected for each soil type (impacted versus unimpacted) —which was set to *k* = 3. This adjustment yielded a final, design-corrected sample size of approximately *n* = 30 households needed to detect the specified effect size with 80% power at the 5% significance level.

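### Equation 1 uses the outcome's own within-household variance as s_x², so m = 13 and the 80% power claimed at 30 households are unsupported

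*Protocol article*

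**What the plan says.** All inputs are in the protocol article, Sample Size Calculations. The target is a meaningful change in soil E. coli "with 80% power at a 5% significance level", over six visits, "three before and three after the intervention".

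Equation 1 is m = 2(z_α + z_Q)²σ²(1−ρ1)/(t s_x² d²). Its inputs are:

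- Total variance σ², which "was calculated as 5.2 log (copies/gram)^2^ based on all available soil samples".
- s², described as the term that "accounts for the variability in repeated measurements within the same location". Its value "was estimated as 4.3 log (copies/gram)^2^ from a mixed-effects model including a random intercept for location".
- The correlation ρ1, "which reflects the correlation of repeated measurements within a single location over time, was estimated to be 0.16".
- The effect d, which "was defined as a 0.45-log (copies/gram) reduction in soil concentrations".

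The result is m = 13. Equation 2 multiplies m by (1+ρ2)(k−1), with ρ2 = 0.17 and k = 3, and gives about 30 "households needed to detect the specified effect size with 80% power at the 5% significance level".

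Data Analysis and Outcomes then plans a regression that estimates a step change, measured against the predicted time trend, and a change in trend.

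**The concern.** The subscript x in the printed equation points to the explanatory variable, but the text defines and enters a variance of the outcome. Outcome variance then stands both above and below the line, and what is left hardly reflects how noisy soil E. coli is. A household count for a fixed log change cannot be obtained that way.

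This calculation is the only quantitative justification in the document for 30 intervention households and for the power of the primary outcome. Anyone interpreting the result, a null result above all, needs to know what change the trial could detect.

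**Working it through.** **Inputs.** σ² = 5.2, s² = 4.3, ρ1 = 0.16, d = 0.45, t = 6 (3 pre, 3 post), ρ2 = 0.17, k = 3, α = 0.05, power 0.80. The protocol does not state sidedness. Two-sided, (1.960 + 0.842)² = 7.849.

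**1. Reproduce the plan.**
m = 2 × 7.849 × 5.2 × 0.84 / (6 × 4.3 × 0.45²) = 68.57 / 5.22 = 13.12. The stated 13 is reproduced; a one-sided z gives 10.3, so the plan used a two-sided test.
n = 13 × 1.17 × 2 = 30.4. The stated 30 is reproduced.

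**2. Why m is not a sample size.**
- σ²(1−ρ1) = 5.2 × 0.84 = 4.368, and 4.368/4.3 = 1.016. What remains is 2 × 7.849/(6 × 0.2025) = 12.9, times 1.016 = 13.1.
- Units: log² cancels log², leaving 1/d², that is 1/log², instead of a count.
- Direction: doubling s² alone to 8.6 lowers m from 13.1 to 6.6, so noisier repeat measurements would call for fewer households.

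**3. What belongs in that place.** For one household with one sample per visit, the post mean minus the pre mean has variance 4.368 × (1/3 + 1/3) = 4.368 × 2/3. This equals 4.368/(6 × 0.25), and 0.25 = 0.5 × 0.5 is the variance of a 0/1 connection indicator over 3 pre and 3 post visits. No factor 2 arises, because each household is its own control.

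**4. Three samples averaged per visit.** The variance of a visit mean is w = 4.368 × (1 + 2ρ)/3. It is 1.456 for independent replicates and 4.368 × 1.34/3 = 1.951 for replicate correlation 0.17.

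**5. Two contrasts.** SE = √(w × c/30), with w = 4.368 for one sample per visit.
- Simple pre/post mean difference: c = 2/3.
- Step change with separate pre and post trends: the post line at its first visit contributes 1/3 + 1/2 = 5/6, and the pre line extrapolated to that visit contributes 1/3 + 4/2 = 7/3, so c = 19/6 = 3.17.

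Power = Φ(0.45/SE − 1.96). Detectable change at 80% power = 2.802 × SE. Households for 80% power = 7.849 × w × c/0.2025, rounded up.

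| Contrast, 30 households | Samples per visit | SE | Power for 0.45 log | Detectable change | Households for 80% |
|---|---|---|---|---|---|
| Pre/post mean | 1 | 0.312 | 30% | 0.87 | 113 |
| Pre/post mean | 3, correlation 0.17 | 0.208 | 58% | 0.58 | 51 |
| Pre/post mean | 3, independent | 0.180 | 71% | 0.50 | 38 |
| Step with trends | 1 | 0.679 | 10% | 1.90 | 537 |
| Step with trends | 3, correlation 0.17 | 0.454 | 17% | 1.27 | 240 |
| Step with trends | 3, independent | 0.392 | 21% | 1.10 | 179 |

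These figures take all of 4.368 as visit-to-visit noise, with no residual autocorrelation and no contribution from the comparison sites.

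**The case against.** The algebra of Equation 1 is hard to defend; the size of the shortfall is open to argument.

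- **Stable spot-to-spot variance.** Soil Sample Collection keeps the same spots at all six visits, so fixed differences between spots cancel in a pre/post contrast. The pilot model had only a location intercept, so 4.3 may include such differences, and the documents give no split. With independent replicates, 80% power for the pre/post mean needs a residual variance of at most 0.45² × 30 × 1.5 × 3/7.849 = 3.48. A stable share of about 20% of 4.368 would be enough, or about 40% at replicate correlation 0.17. This stands, so 58% to 71% is conditional. It does not rescue the step change: the limit there is 0.45² × 30 × 3/(7.849 × 19/6) = 0.73, a stable share of about 83%.
- **Meaning of ρ2.** The protocol does not say which component of the location-and-date model gives 0.17. If it is the location share, using it as replicate correlation counts it twice. The 58% end rests on that reading.
- **x as visit number.** Then s_x² would be 2.92 and d a slope of 0.45 log per visit, and 30 households would suffice. The text defines d as a change in concentration and s² as variability of repeated measurements, so it does not support this reading.
- **Equation 2 compensates.** Its multiplier is 2.34, where the usual design effect 1 + ρ2(k−1) is 1.34. That enlarges n, but the powers above are computed directly at 30.

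A reader might also infer more than the documents carry. Putting 0.25 into Equation 1 unchanged gives 226, and Equation 2 as printed then gives 226 × 2.34, about 528. Neither is the number needed: both keep a factor 2 that does not belong to a one-group contrast, and neither credits the averaging of three samples. Nor is it fair to say that m ignores noise under every reading. It is constant when both variances scale together at fixed d, but d was set at 20% of the pilot SD, and with a standardised effect a correct formula would be constant too. The units and direction checks are the sound ones.

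**Conclusion.** The point holds. The arithmetic reproduces, but an outcome variance was entered where the variance of the exposure is needed, so neither m = 13 nor 80% power at 30 households follows for a 0.45-log change.

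On the plan's own inputs, the pre/post mean difference falls moderately short of 80%, and stable spot-to-spot variance could close that gap. The planned step change falls far short, and only an extreme variance split would close it. The exact size depends on how the three samples are combined, on replicate correlation, on the stable spatial share and on which coefficient is tested.

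The documents do not support reading this as a demand for hundreds of households, or as proof that the trial is uninformative. They also do not say that a null result would be taken as evidence of no effect; that is a risk of leaving the stated power uncorrected.

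**What to change.** In Sample Size Calculations:

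1. Define s_x² as the variance of the connection indicator and set it to 0.25 for three pre and three post visits.
2. Drop the factor 2 for the single-group contrast.
3. Replace Equation 2 by the variance of a mean of k samples, (1 + (k−1)ρ2)/k, and say what ρ2 measures. Steps 1 to 3 must be made together: changing 0.25 alone leads to the figure of about 528.
4. Keep 30 households. Restate power or detectable change for the coefficient to be tested under Data Analysis and Outcomes. Give the simple pre/post figure only if that contrast is made primary.
5. State the assumptions on replicate correlation and on stable spot-to-spot variance. Preferably take the variance components from culturable soil E. coli in the pre-connection rounds, under way since August 2024, in place of the ybbW gene-copy proxy.

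The cost is a short recalculation, revised wording and a less favourable stated power. No household or visit is added.

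### Equation 2 misplaces the brackets in the clustering design effect (2.34 instead of 1.34), and the stated 30 households are reached only through that wrong factor

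*Protocol article*

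**What the plan says.** The section Sample Size Calculations works in two steps. Equation 1 gives a crude number of households, m, for six visits per household ("three before and three after the intervention"), sized "with 80% power at a 5% significance level". The result reported is m = 13.

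Equation 2 then adjusts for the clustering of soil samples within sites. It is printed as n = m × ((1 + ρ₂) × (k − 1)). The correlation ρ₂ "used in this adjustment was estimated as 0.17 from a model based on the preliminary data set", and k = 3 is the number of soil samples of each soil type at a visit. The section closes: "This adjustment yielded a final, design-corrected sample size of approximately" n = 30 households.

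This is the article's only stated justification for the number of households behind the primary outcome. It agrees with the enrolment plan: 50 households, of which 20 are comparison sites, leaves 30.

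**The concern.** A clustering adjustment has to leave the sample size alone when there is nothing to adjust for, that is, when each visit yields one sample (k = 1) or the samples within a cluster are uncorrelated (ρ₂ = 0). The printed factor does neither. It resembles the usual design effect, 1 + ρ₂(k − 1), with the brackets moved so that the 1 is also multiplied by k − 1.

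If the slip were only in the typesetting, it would not matter. If it was carried into the calculation, the household target and the power attached to it come from an invalid expression, and the 80% is not the power that the plan's own inputs imply for 30 households.

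**Working it through.** **Inputs, all from Sample Size Calculations**

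- Total variance σ²: "was calculated as 5.2 log (copies/gram)^2^ based on all available soil samples"
- Within-household variance, used as s_x² in Equation 1: "was estimated as 4.3 log (copies/gram)^2^ from a mixed-effects model including a random intercept for location"
- Repeated-measures correlation ρ₁: "was estimated to be 0.16"
- Effect size d: "was defined as a 0.45-log (copies/gram) reduction in soil concentrations"
- t = 6, ρ₂ = 0.17, k = 3
- 80% power and 5% significance. Sidedness is not stated; two-sided is taken here because it reproduces m.

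**Step 1. Reproduce m.** Equation 1 is m = 2(z_α + z_Q)² σ²(1 − ρ₁) / (t s_x² d²).

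- Numerator: 2 × (1.960 + 0.842)² × 5.2 × 0.84 = 68.57
- Denominator: 6 × 4.3 × 0.45² = 5.2245
- m = 13.12, matching the stated 13. A one-sided 5% level gives 10.34, which does not match.

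**Step 2. Reproduce n from Equation 2 as printed.**

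- Factor: (1 + 0.17) × (3 − 1) = 2.34
- n = 13 × 2.34 = 30.4 (30.7 from unrounded m), matching the stated figure of about 30.

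**Step 3. Test the factor at its limits.**

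| Case | Printed (1 + ρ₂)(k − 1) | Design effect 1 + ρ₂(k − 1) |
|---|---|---|
| k = 1, ρ₂ = 0.17 | 0 | 1 |
| k = 2, ρ₂ = 0.17 | 1.17 | 1.17 |
| k = 3, ρ₂ = 0.17 | 2.34 | 1.34 |
| k = 3, ρ₂ = 0 | 2 | 1 |

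The two forms agree at k = 2 but not at the k = 3 used here.

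**Step 4. Apply the design effect to the plan's own m.**

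- n = 13 × 1.34 = 17.4, rounded up to 18 (17.6 from unrounded m).
- The printed multiplier is 2.34 / 1.34 = 1.75 times the correct one.

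**Step 5. Power on Equation 1 as printed, with the 1.34 factor.** Solving Equation 1 for the standardised effect gives λ = √[(n / 1.34) × 5.2245 / (2 × 5.2 × 0.84)], and power = Φ(λ − 1.96).

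- n = 30: λ = √(22.39 × 5.2245 / 8.736) = 3.66, power about 96%.
- n = 18: λ = √(13.43 × 5.2245 / 8.736) = 2.83, power about 81%.

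**Step 6. Why Step 4 is not the final answer.** In Equation 1 as filled in, σ² and s_x² are both in squared log units and cancel, so m is left proportional to 1/d² and would change with the base of the logarithm. A number of households cannot depend on that. The units balance if s_x² is the variance of the covariate whose coefficient is d. The article does not give the coding of that covariate, so the following only shows the range, with every other input unchanged:

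- Pre/post indicator, three visits each side: s_x² = 0.25, m = 13.12 × 4.3 / 0.25 ≈ 226, and × 1.34 ≈ 302.
- Time coded 1 to 6: s_x² = 35/12 = 2.92, m = 13.12 × 4.3 / 2.92 ≈ 19, and × 1.34 ≈ 26. Here d would be a change per visit.

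**The case against.** The best defence is that the error is harmless. Taken by itself, it asks for more households than the corrected formula does, and 30 remain planned. That is right about direction: a reader might infer that the bracket error leaves the study underpowered, and the documents do not support that. The defence reassures only if Equation 1 is sound, which Step 6 puts in doubt.

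A reader might also infer that 30 cannot be obtained from the plan's inputs. It can: both printed equations reproduce the stated figures. What fails is the validity of the second equation. For the same reason, the slip cannot be put down to typesetting, because 1.34 does not lead to 30.

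A further tempting step is to divide by k, since each household supplies three samples per visit while m counts households; that would give 13 × 1.34 / 3 = 5.8. The article does not establish what this needs. Under Soil Sample Collection, the three samples at straight-pipe or cesspool sites are taken at the point of impact and at two set distances from it, so they are not plainly exchangeable replicates. The model behind ρ₂ has random intercepts for location and sampling date, so whether ρ₂ is the correlation among samples within a visit is unclear. Equation 1 also already carries (1 − ρ₁), which may change if samples are averaged within a visit.

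Nor do the documents support a single replacement such as 50 households. That figure needs a pre/post covariate, removal of the factor 2 in Equation 1 (226 / 2 = 113), and division by k (113 × 1.34 / 3 ≈ 50).

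**Conclusion.** The point holds for Equation 2. Its multiplier is 2.34 where the design effect is 1.34, and the wrong expression was computed, not merely misprinted. With the plan's m = 13, the corrected requirement is about 18 households against the stated 30; equivalently, 30 households have about 96% power against the stated 80%. Both figures assume Equation 1 as printed, a two-sided 5% level, and ρ₂ = 0.17 as the correlation relevant to the k = 3 samples.

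Those figures measure the size of this one error. They are not a recommended sample size or a power claim, because the use of 4.3 as s_x² is itself doubtful and the result moves from about 26 to about 302 households under two plausible codings. The firm conclusion is that the power now attached to 30 households rests on an invalid formula and has to be recalculated.

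**What to change.** - Replace Equation 2 with n = m × [1 + ρ₂(k − 1)].
- In Equation 1, state which covariate s_x² refers to and how it is coded, check whether 4.3 belongs there, and recompute m.
- Say how the three samples per visit enter the primary analysis (averaged, modelled individually, or otherwise) and what ρ₂ measures, so that the clustering factor matches that analysis.
- Restate the power, or the detectable effect at 80% power, for the 30 intervention households already planned.

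The cost is one corrected equation, one rechecked input and a rewritten closing sentence. The correction requires no new data and no change in enrolment.
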